#### Safety information of drugs targeting the ACE2 domain:

For patients with COVID-19 disease we can indicate the following with regards to safety in the ACE2 domain: Icatibant treatment was well-tolerated in all 10 patients who received icatibant for COVID-19 disease. The adverse event most commonly reported was pain at the site of injection. These effects were temporarily and resolved without need of treatment. A slight increase of less than threefold upper limit of normal of AST and ALT was observed with icatibant treatment. This side effect is commonly observed in patients treated with icatibant. All liver function test resolved spontaneously and no additional intervention was needed. No serious adverse events were observed.

We do not expect specific COVID driven toxicity.

## 5. Trial drugs

### 5.1 Identity of investigational product(s)

Lanadelumab has a marketing authorisation in the European Union. Takeda will provide sufficient quantities of fully characterized investigational medicinal products prepared in accordance with Good Manufacturing Practice (GMP), properly packaged and labelled.

The trial drugs will be accounted for in a drug inventory and stored at appropriate conditions (intravenous solution has to be stored in the refrigerator preferably in a locked safe, until used in the trial. Excess trial medication will be returned to the sponsor. The study pharmacist will supervise the storage of all trial medication.

The following formulations will be used:

Name : Takhzyro®

Active ingredient : lanadelumab

Excipients : Disodium phosphate dihydrat, Citric acid monohydrate, Histidine, Sodium chloride, Polysorbate 80, Water for injections

Dosage form : 2 ml of solution in a vial (type I glass) with a coated butyl rubber stopper and an aluminium seal with violet flip-off cap. This will be reconstituted with sodiumchlorde 0,9% to a final concentration of 3.0 mg/mL. Lanadelumab will be given over an inline filter of 0.2 µm.

Strength : 300mg

Manufacturer : Takeda / Shire.

### 5.2 Packaging and labelling of trial medication

Trial medication will be supplied as the commercially available lanadelumab. These vials will be used during the trial. Since this is an open trial, blinding procedures are not applicable. The containers will be labelled with: sponsor's name and contact details / phone number, protocol number, name study, drug name, number of capsules and strength dose, instructions for use, batch number, storage conditions, expiry date, "For clinical trial use only", "Keep out of reach of children" in concordance with GMP annex 13 legislation. In addition, the investigational staff will label the containers and package with subject code / randomisation number.

### 5.3 Method of assigning subjects to treatment groups

Subject will be randomized in a 1:1 ratio to receive lanadelumab or standard clinical management without drug intervention. Each group will contain 20 participants.

Randomization will be done by Castor. Each patient will be entered into the Castor system and randomization will be allocated immediately. This is a standard procedure as deployed in other trials.

Each site has drug on site for at least one patient and therefor randomisation to the intervention arm can be acted upon immediately. Considering the small sample size there will be no stratification.

#### **5.4 Selection and timing of dosing and dietary**

Explanation of the dosing scheme is provided in the protocol. No restrictions are applicable to dietary.

#### **5.5 Treatment Compliance**

All administration of medication is supervised and recorded by the study personnel. The Investigator or his/her designee will maintain an adequate record of the receipt and distribution of all study supplies. These forms will be available for inspection at any time.

#### **5.6 Drug accountability**

The investigator or designee (i.e., pharmacist) is responsible for ensuring adequate accountability of all used and unused study drugs. Dispensing records will document quantities received from the CTU and quantities dispensed to subjects, including lot number, date dispensed, subject identifier number, subject initials, and the initials of the person dispensing the medication.

At study initiation, the monitor will evaluate and approve the site's procedure for study drug disposal/destruction in order to ensure that it complies with GCP requirements. If the site cannot meet GCP requirements for disposal/destruction, arrangements will be made between the site and the sponsor or its representative, for return of unused study drug supplies.

During the study the drugs will be stored at the site. Drug storage will also be evaluated at the initiation of the study.

Prior to disposal/destruction or return of used, unused, and depleted containers, final drug accountability and reconciliation will be performed by the monitor.

All drug supplies and associated documentation will be regularly reviewed and verified by the monitor.

#### **5.7 Prior and Concomitant Therapy**

For two weeks preceding day 1 and during the study, all concomitant medication will be recorded in the subject's Case Report Form (CRF). All medication is allowed during this trial except for experimental drugs listed in the exclusion criteria.

## 6. Study procedures

### 6.1 Inclusion Screening and screening during treatment

At inclusion screening the medical history of the subject will be verified and documented to establish eligibility for inclusion. In table 2 a summary is listed of the parameters that should be collected at baseline and while on treatment.

Table 1: summary of study procedures during the study

|                                                    | At inclusion | Day 1 | 2 | 3 | 4 | 5 | 6 | 7 | 8-14 | >14 |
|----------------------------------------------------|--------------|-------|---|---|---|---|---|---|------|-----|
| Demographics a                          | X            | X     |   |   |   |   |   |   |      |     |
| Physical examination b                  | X            | X     |   |   |   |   |   |   |      |     |
| Laboratory tests c                      | X            | X     | X | X | X | X | X | X | X    | X   |
| Administration lanadelumab intervention group only |              | X     |   |   | X |   |   |   |      |     |
| Oxygen need d                           | X            | X     | X | X | X | X | X | X | X    | X   |
| Concomitant medication                             | X            | X     | X | X | X | X | X | X | X    | X   |
| Clinical outcome                                   | X            | X     | X | X | X | X | X | X | X    | X   |
| PK e                                    |              | X     | X | X | X | X | X | X | X    |     |
| PD & in depth sampling f                |              | X     |   |   | X |   |   |   |      |     |

a: sex, age, BMI, days of illness, Charlson Comorbidity Index (CCI), comedication, CT severity score, oxygen saturation without supplementation, oxygen supplementation need, respiratory rate at baseline.

b: respiratory rate, oxygen saturation, and supplemental oxygen.

c: hemocytometry, WBC differentiation, D-dimer, ferritin, CRP, and albumin. EDTA plasma 10 mL and citrate 4 mL for plasma kallikrein metabolites.

d: change in oxygen need and oxygenation expressed as absolute number of liters per hour using a target oxygenation of above 94% as a marker of pulmonary status. ICU admission after admission to the ward, changes in D-dimer relative to baseline, PKa metabolites changes relative to baseline, safety.

e determination of lanadelumab plasma concentration (pk outcome, intervention group only) and bradykinin markers (PD outcome. ) PK after first lanadelumab administration: T1=12-24; T2 = T1 + 24 (+/-6 hours); T3= T1+ 48 (+/-6 hours); T4= T1 + 72 (+/-6 hours); T5= T1 + 96(+/-6 hours); T6 = T1 + 120 (+/-6 hours); T7 = T1 + 144 (+/-6 hours) and then daily. If only one lanadelumab dose is given PK will be sampled up to and including day 7, or until patient is dismissed from the hospital whichever comes first.

f Determination of bradykininemarkers and in-depth sampling. Labsampling day 1 needs to be done before first administration of lanadelumab. Day 4 has a window of +/- 2 days if day 4 is in the weekend. Blisters for day 1 and 4 include 2x 10 ml EDTA, 2x 4 ml citrate and 1 PAXgene for in depth labanalysis., See also the labmanual.

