| Risk analysis                                                                                          | The risk-classification is assessed as low / moderate to the study population receiving study drug at the current regimen. Lanadelumab has a favorable safety profile and is approved by the Dutch medicines evaluation board for the dose administered. Therefore the risk for adverse events is low.                                                                                                                                                                                                                                                                                                                                                                                                                                                                                                                                                                                                                                                                                                          |
| Nature and extent of the burden and risks associated with participation, benefit and group relatedness | 
The study participants are COVID-19 patients that might benefit from the participation in this clinical trial.
 
Participants are on the ward of the time of study
 
Burden: short visits (15 minutes) several time per day on the ward by doctor and nurse for clinical evaluation. The duration of the entire trial (excluding screening period) is 14 days. Duration of treatment with study medication is 2 days.
 
Lanadelumab has a generally favorable safety profile. We refer to the SmPC for most common side effect.
 
For pharmacokinetic purposes 14 blood samples will be taken in total in the intervention group only. For a total of 28 mL. Additional samples will be taken for biomarker evaluation (two occasions of 40mL each).
 
Safety assessment (haematology, clinical chemistry, blood glucose tests, hCG blood and hCG urine tests, serology) will be collected as part of routine care. The total blood volume taken will be approximately 100 mL..
 |

| ANALYTICAL AND
STATISTICAL
METHODS |                                                                                                                                                                                                                         |

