|---------------------------------------------------|-------------------------------------------------------------------------------------------------------------------------------------------------------------------------------------------------------------------------|
| Bioanalysis                                | Plasma concentrations of lanadelumab will be performed via Takeda through the commercial lab that has performed sample measurements in their clinical trial.                                                            |
| Pharmacokinetics                           | Non-linear mixed effect modelling will be deployed by the department of Pharmacy and the Radboud Applied Pharmacometrics group.                                                                                         |
| Safety and
demographics                | Tabulation and descriptive statistics for subject characteristics. Tabulation of adverse events, vital signs and biochemistry and haematology data.

Statistical evaluation will be supervised by [name]. |

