#### 3.3 Exclusion criteria

Subjects who meet any of the following criteria will be excluded from participation in this study:

1. Has previously participated in this study
2. Acute myocardial or cerebral ischemic event at time of enrolment
3. Receiving an agent that is specified as an intervention in this domain as a usual medication prior to this hospitalization will exclude a patient from receiving that agent
4. A baseline alanine aminotransferase or an aspartate aminotransferase that is more than five times the upper limit of normal
5. Patient is known hypersensitive to full human monoclonal antibodies.
6. Patient is pregnant or breast feeding

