### 4.3 Safety and potential risks

For general safety information we refer to the SmPC of lanadelumab.

Briefly stated it has the following information:

Hypersensitivity is an important identified risk and is discussed in the warnings and precautions of the reference labelling. In case of a severe hypersensitivity reaction, administration of TAKHZYRO must be stopped immediately and appropriate treatment must be initiated.

Immunogenicity is an important potential risk for lanadelumab and is monitored closely. The known potential risks of disordered coagulation associated with monoclonal antibodies have been characterized and no unexpected signals were identified.

The most commonly occurring adverse events with greater frequency in the lanadelumab treatment groups were injection site reactions (34.1% placebo, 52.4% lanadelumab) and dizziness (0% placebo, 6.0% lanadelumab). Less common reactions in the lanadelumab group compared to placebo include hypersensitivity (1% vs. 0%), increased liver enzymes (2% compared to 0%). An open-label extension study to evaluate the long-term safety and efficacy of lanadelumab for prevention of HAE attacks is ongoing. (Riedl et al., 2017). Pharmacokinetic analyses showed that the use of concomitant medications such as analgesic, antibacterial, antihistamine, anti-inflammatory, and antirheumatic medications used in the treatment of HAE had no effect on the pharmacokinetic properties of lanadelumab, suggesting that the drug-drug interaction potential of those evaluated drug classes is low. Similar observations were made for rescue medications, including plasma-derived and recombinant C1-INH, ecallantide, and icatibant, used for acute treatment of HAE attacks.

In this study two dosages of 300 mg intravenous lanadelumab are given on day 1 and day 4. The cumulative dose of 600 mg per week is higher than the current licensed dose for prevention of HAE. Even with a second dose given on day 4 of treatment the predicted drug concentrations remain far below the maximal tolerable dose. [see pop-PKPD modeling file with simulations]. We do not expect additional toxicity of the approach chosen.

Additional safety information to support for lanadelumab given as intravenous administration

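### Safety of intravenous lanadelumab is a primary objective, yet the schedule fixes no post-baseline ALT/AST and no blood pressure or heart rate in either arm

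*Protocol*

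**What the plan says.** Section 1.3 and the Synopsis give two primary objectives; the second is to show that intravenous lanadelumab is safe in COVID-19. Section 1.2 says the intravenous route was not tested in the clinical package for hereditary angioedema.

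On risks, section 4.3 states "Hypersensitivity is an important identified risk and is discussed in the warnings and precautions of the reference labelling" and lists "increased liver enzymes (2% compared to 0" percent, lanadelumab against placebo. Section 3.3 excludes patients with "A baseline alanine aminotransferase or an aspartate aminotransferase that is more than five times the upper limit of normal".

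On measurements:

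- Table 1, laboratory row: "c: hemocytometry, WBC differentiation, D-dimer, ferritin, CRP, and albumin", plus plasma for kallikrein metabolites. It is marked in every column from inclusion to beyond day 14.
- Table 1, physical examination row: "b: respiratory rate, oxygen saturation, and supplemental oxygen". It is marked at inclusion and day 1 only.
- Section 6.1, Data and outcome variables: the same three respiratory items are registered around administration and daily thereafter, and the same laboratory list is repeated.
- Section 6.2: one sentence saying that safety assessments are recorded, with no list and no times.
- Synopsis, burden and risks: haematology, clinical chemistry and other safety tests "will be collected as part of routine care".
- Synopsis, Safety and demographics: "Tabulation of adverse events, vital signs and biochemistry and haematology data".

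**The concern.** The protocol promises safety tables whose inputs it does not schedule. Liver enzymes are a named risk and an eligibility criterion, but no follow-up ALT or AST is fixed. Vital signs are to be tabulated, but only respiratory items are listed.

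What is at stake is whether the two arms can be compared on safety. If liver tests and circulatory readings exist only when a clinician asks for them, their number and timing can differ by arm, because the treating staff know who received the drug. The adverse-event rule in section 6.3 adds to this: an event is recorded only if there is reasonable suspicion that the study medication caused it. Controls receive no study medication, so adverse-event counts can hardly be compared between arms. Objective measurements at fixed times in both arms are then the main comparative safety evidence available. An analysis plan cannot recover values that were never collected.

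**Working it through.** The protocol gives no figure to reproduce on this point, so the check sets each risk or promised table against the schedule.

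**1. Liver enzymes**
- Needed by: section 4.3 (2% against 0%), section 3.3 exclusion 4, and the Synopsis biochemistry table.
- Scheduled: the laboratory row is marked in 10 columns (inclusion, days 1 to 7, days 8–14, beyond day 14). ALT/AST are listed in 0 of 10.
- Elsewhere: exclusion 4 cannot be applied without a baseline value, so one must exist in both arms. Nothing comparable requires a later value. The routine-care sentence names clinical chemistry only as a category and gives no times.
- Result: a baseline is implied but has no line in the schedule; no post-baseline value is fixed in either arm.

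**2. Blood pressure and heart rate**
- Needed by: the Synopsis vital-signs table. Their relevance to a hypersensitivity reaction is a clinical inference; section 4.3 does not name a haemodynamic risk.
- Scheduled: neither appears in Table 1, its footnotes or the rest of section 6.1. The list under Data and outcome variables is worded as examples, so it does not forbid other readings, but it does not call for them.
- Result: planned infusions = 20 treated patients × 2 (days 1 and 4) = 40; fixed blood pressure or heart rate readings around them = 0. Controls also have none.

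**3. Examination at the second infusion**
- Table 1 leaves day 4 unmarked in the physical examination row.
- Data and outcome variables registers all three footnote b items before and after administration and daily.
- Result: the respiratory items are covered on day 4. Only the table mark is missing.

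**4. What discretionary testing does to a comparison**
- Let p be the true proportion with a raised value in both arms, and let a and b be the proportions tested in the treated and control arms, with testing unrelated to the value.
- Detected proportions are p × a and p × b, with ratio a/b.
- With no true difference between arms, the observed ratio equals the ratio of testing rates. The protocol fixes neither a nor b. It does not say they will differ, and the direction is unknown; fixed testing in both arms sets both near 1.

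**The case against.** The strongest reply is that this is a small, pragmatic trial in ward inpatients. Chemistry is addressed through routine care, staff assess patients several times a day, Table 1 is only a summary, and screening plus the monitor's eligibility check (section 10.2) should secure a baseline ALT/AST. Much of this stands. Using routine-care data is a legitimate choice, and a baseline transaminase is required if exclusion 4 is applied. What it does not supply is any analyte or time point after baseline, or any blood pressure or heart rate entry.

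Several stronger readings are tempting but not supported:

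- *That Table 1 captures nothing relevant to the named risks.* D-dimer is measured daily, and respiratory rate and saturation, which bear on an infusion reaction, are registered around dosing.
- *That no examination takes place at the second infusion.* Section 6.1 covers the three respiratory items then.
- *That clotting times must be added.* Section 4.3 says the coagulation risk has been characterised without unexpected signals. Adding PT/aPTT would be a preference.
- *That the 2% rate gives the size of the gap.* The chance of at least one case in 20 is 1 − 0.98^20 = 33%, but this carries a subcutaneous rate from another disease into this trial and does not say how many cases would go unseen.
- *That the icatibant findings show a liver signal here.* Section 4.3 reports rises below three times the upper limit of normal that resolved spontaneously, with a different drug.

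A reader may also notice "Immunogenicity is an important potential risk for lanadelumab and is monitored closely" and the absence of any patient anti-drug-antibody sample. That sentence sits in a summary of the product information and may describe the product rather than this trial, so the present point does not rest on it.

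**Conclusion.** The point holds in this form. For a primary safety objective, the protocol fixes no ALT/AST after baseline and no blood pressure or heart rate at any time, in either arm, while planning tables of biochemistry and vital signs. The sections cited need to be reconciled.

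The size is a count of scheduled data: 0 of 10 laboratory columns for ALT/AST, and 0 fixed circulatory readings around 40 planned infusions. The effect on the results cannot be quantified from the protocol, because testing rates under routine care are not given. The conclusion assumes that Table 1 and section 6.1 are the operative schedule and that routine testing may vary between patients or arms; it does not assume that it will. The change should be made before data collection, since the loss cannot be repaired afterwards.

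**What to change.** - Table 1, footnote c, and the matching list under Data and outcome variables: add ALT and AST at inclusion, recording the value used for exclusion 4, and on fixed days in both arms. Use blood already drawn for the laboratory row.
- Table 1, footnote b, and Data and outcome variables: add blood pressure and heart rate, recorded before and after each infusion and at matched times on days 1 and 4 in controls.
- Table 1, physical examination row: mark day 4 so that it agrees with the text of section 6.1.
- Synopsis, burden and risks: state that routine-care results supplement these scheduled items.

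The cost is a few routine analytes, bedside readings and slightly more data entry. No dose, eligibility threshold or clinical rule changes.

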### 3. Subject population

#### 3.1 Number of subjects and subject selection

Fourty patients will be randomized 1:1 for the intervention with lanadelumab iv. Twenty SARS-COV2 positive patients treated with lanadelumab 300 mg IV on day 1, followed by a second dose of lanadelumab 300 mg IV on day 4. The other 20 lanadelumab patients will receive the same treatment algorithm while NOT receiving lanadelumab. The estimated number of patients being treated for COVID disease is difficult to predict. Currently about 20% of the COVID-19 patients are hospitalized and out of these patients about 20% is admitted to the ICU.

These will be patients from the following centers:

- Amsterdam UMC, Amsterdam
- Radboud University Medical center, Nijmegen,
- University Medical Center Utrecht, Utrecht,
- Rijnstate Hospital, Arnhem
- Flevoziekenhuis, Almere

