#### 3.5 Removal of subjects from the study

The investigator may terminate participation if:

- There is violation of protocol
- It is in the best interest of the subject
- Patients that are transferred to the ICU will be followed up for safety and if possible samples will be taken, but are considered to have reached a study endpoint.

Subjects dropping out before the final dose has been given, will not be replaced. Patients are regarded evaluable after both treatment days are completed.

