### **7.3 Statistical analysis**

Statistical analysis will be performed using descriptive statistics for tabulation of population as well as results. [name] from our department of health evidence will help with the statistical analysis. Appropriate test will be deployed.

For the primary endpoint we intend to collect repeated measurements of oxygen use in L/min and therefore any significant decline in a patient's health should be reflected in these repeated measurements. We acknowledge that missing data due to death is a potential source of bias, particularly if oxygen is stopped at the point where a significant decline is observed. Therefore, a worst-case scenario sensitivity analysis, in which the highest value of oxygen recorded for any patient is imputed for patients with missing data following their death. Other valid methods to account for missing data due to death will be investigated and included in the Statistical Analysis Plan.

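### ICU admission is an outcome on its own and death is not counted in it, so a ward death without ICU transfer reads the same as recovery on that outcome

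*Protocol*

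**What the plan says.** The primary endpoint is set in section 7.3: "For the primary endpoint we intend to collect repeated measurements of oxygen use in L/min". Footnote d to Table 1 in section 6.1 belongs to the oxygen row. After oxygen need it adds further items, the first of which is "ICU admission after admission to the ward"; the others are change in D-dimer, change in PKa metabolites, and safety. Section 3.5, on removal of subjects, keeps patients who go to the ICU under safety follow-up, with samples if possible, and says that they "are considered to have reached a study endpoint". No other event is given that status.

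Death appears in two roles. In section 6.3 it is a criterion for a serious adverse event, and its causality has to be assessed. In section 7.3 it is a source of missing oxygen data: "We acknowledge that missing data due to death is a potential source of bias". That section plans a worst-case sensitivity analysis in which "the highest value of oxygen recorded for any patient is imputed for patients with missing data following their death", and leaves other methods for data missing through death to the statistical analysis plan. Neither provision refers to the ICU outcome. Table 1 also has a row for clinical outcome at every time point, but does not say what it contains.

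**The concern.** A patient who dies on the ward can no longer be admitted to the ICU. If the event is ICU admission alone, that patient is counted with those who recovered. Section 1.2 gives the aim of treatment as preventing progression to severe disease, ARDS and prolonged ventilation. A ward death is a failure on that aim, but the ICU outcome as listed does not register it.

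Ward death without ICU transfer is possible under this protocol. The eligibility criteria in sections 3.2 and 3.3 set no upper age limit and do not exclude patients for whom ICU care has been ruled out. Footnote a, the list of baseline items, does not mention such a decision. The trial is open-label and section 5.3 rules out stratification. At stake is the ICU comparison: an arm with more ward deaths could show fewer ICU admissions, and a descriptive table of ICU counts would then favour the arm that did no better, or did worse.

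**Working it through.** The protocol gives no sample size calculation, test or expected difference for this outcome, so there is no figure of its own to reproduce. The check is on direction and size.

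**Inputs**
- Arm size: 20 per arm (section 5.3).
- Background ICU rate: section 3.1 says of hospitalised COVID-19 patients that "out of these patients about 20% is admitted to the ICU". That gives 0.20 × 20 = 4 patients per arm. The trial's patients are selected on oxygen need, so 6 of 20 (30%) is shown as a second case; that figure is an assumption.
- Ward deaths without ICU transfer: not given. Assumed to be 1 to 3 patients in one arm, or a proportion d of 5% to 20%.

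**Step 1: ward deaths that replace ICU transfers.** Each displaced transfer changes the arm's ICU rate by 1/20 = 5 points. Let the same number m deteriorate in both arms, and let k of the m in arm A die on the ward. ICU admission alone is (m − k)/20 in arm A and m/20 in arm B. ICU admission or death is m/20 in both.

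| m | k | ICU alone, A vs B | Fisher p | ICU or death, A vs B |
|---|---|---|---|---|
| 4 | 1 | 15% vs 20% | 1.00 | 20% vs 20% |
| 4 | 2 | 10% vs 20% | 0.66 | 20% vs 20% |
| 4 | 3 | 5% vs 20% | 0.34 | 20% vs 20% |
| 6 | 1 | 25% vs 30% | 1.00 | 30% vs 30% |
| 6 | 2 | 20% vs 30% | 0.72 | 30% vs 30% |
| 6 | 3 | 15% vs 30% | 0.45 | 30% vs 30% |

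ICU admission alone shows a difference of 5, 10 or 15 points where the arms have equal numbers of bad outcomes.

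**Step 2: ward deaths that are additional.** Let a proportion d of one arm die on the ward before any ICU transfer, independently of a 20% ICU risk. Expected ICU rate = 0.20 × (1 − d). Expected ICU-or-death rate = 1 − 0.80 × (1 − d).

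| d | ICU alone | ICU or death |
|---|---|---|
| 0% | 20% | 20% |
| 5% | 19% | 24% |
| 10% | 18% | 28% |
| 15% | 17% | 32% |
| 20% | 16% | 36% |

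As ward deaths rise, the ICU rate falls slightly while the combined rate rises. An arm with d = 10% against one with d = 0% reads 18% versus 20% on ICU alone and 28% versus 20% on ICU or death: the two measures point in opposite directions.

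**The case against.** The strongest reply is that no rule for scoring the ICU item is written. Footnote d is a list attached to the oxygen row, the sentence in section 3.5 may only mark the end of ward follow-up, and the undefined clinical outcome row may capture death. How a competing event enters a non-primary outcome is often left to the statistical analysis plan. This stands in part: that a ward death counts as no ICU event follows from the literal wording, not from a stated rule. But the protocol has already chosen the event, and the deferral in section 7.3 concerns data missing through death for the oxygen endpoint.

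A second reply is that deaths will be visible as serious adverse events. They should be, so a reader who infers that the protocol ignores death would be wrong. That reporting does not enter the ICU comparison, however. Ordinary adverse events are recorded only where the study drug is reasonably suspected, and ICU admission for respiratory insufficiency is not reported as a serious adverse event. ICU transfers and deaths would therefore not appear together in the safety data.

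A third reply is that differences of this size would not be significant: the Fisher p values above run from 0.34 to 1.00. That is correct. But section 7.3 plans descriptive statistics and the synopsis calls the study hypothesis-generating, so raw counts are what readers will judge.

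A reader might also infer that the primary result is exposed in the same way, or that chance imbalance in patients ruled out for ICU will often distort the trial. The first is not supported, because the oxygen endpoint has a sensitivity analysis that penalises death. The second is not supported either: the documents give no rate of such decisions, and only those patients who also deteriorate affect the ICU count. At the 20% rate, an imbalance of 4 such patients would shift the expected count by about 4 × 0.20 = 0.8 of a patient.

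**Conclusion.** The concern holds for the ICU outcome and no further. The protocol makes ICU admission alone an outcome item, calls ICU transfer and no other event a study endpoint, and does not count death in that outcome. Taken as written, a ward death without ICU transfer is a non-event. Each one that replaces an ICU transfer is worth 5 points in an arm of 20, and two make equal arms read 10% versus 20%. The direction follows from the definition; the death counts and the independence in step 2 are assumptions, and the 20% rate is the protocol's figure for hospitalised patients in general. The documents do not show that such deaths will be more frequent in one arm. The change is worth making before the data are read, because the outcome is descriptive, the counts will be small, and a better definition costs little.

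**What to change.** In footnote d and section 3.5, define the outcome as ICU admission or death from any cause, counted from randomisation over one stated follow-up window that is the same in both arms. The window has to be settled first: the synopsis gives 14 days, section 3.4 gives the length of the hospital stay, and Table 1 has a column beyond day 14.

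Analyse the outcome in all randomised patients. Section 3.5 regards patients as evaluable once both treatment days are completed, which could remove an early death from the count. Show ICU admission and death separately by arm beside the combined figure. Add one baseline item, completed before randomisation, that records whether a decision against ICU admission exists.

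The cost is a sentence in each of the two sections and one field on the case report form; ICU transfers and deaths are already to be recorded. The drawback is that the composite joins events of different weight, which is why both components must be shown.
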